**Fig. 1 Fig1:**
[figure not shown]
Schedule of enrolment, interventions, and assessments. *Only applicable for control/nonintervention groups samples. NA = not applicable

At the enrolment visit, female partners who opt to participate and are not actively menstruating will complete a questionnaire regarding genital symptoms and their menstrual cycle; they will self-collect undiluted female genital secretions using a cervicovaginal SoftCup, as well as two vaginal swabs, and provide a first void urine sample for STI testing and 6–8 ml of venous blood. Syndrome-based and PCR-based STI diagnosis and treatment are offered free of charge for all female participants. These study procedures are repeated at the time of her male partner’s PC procedure 4 weeks later.

## Biological sample processing

### Blood collection and processing

Peripheral venous blood is drawn in two Becton Dickinson Vacutainer^®^ acid citrate dextrose tubes. Plasma is isolated by centrifugation and stored at –80 °C for later confirmation of HIV and other tests including herpes simplex virus type 2 and syphilis.

### Genital swab collection and handling

Pre-moistened swabs are carefully applied to the coronal sulcus (two swabs), inner foreskin (two swabs) and urethral meatus (one swab) for men, while dry swabs are availed to women for two self-collected vaginal swabs. All swabs will be placed in clean microtubes/filter tubes and transported to the laboratory on ice. One unprocessed swab (from the inner foreskin and coronal sulcus) will be frozen as is at –80 °C while the others (from the urethra, inner foreskin and coronal sulcus) will be resuspended and stored at –80 °C in two aliquots each of 250 μL phosphate-buffered saline (PBS) mixed with a protease inhibitor and buffer.

### Cervical secretions collection

A flexible plastic cup (Softcup™, Instead) is self-inserted into the vagina and removed after 20 min. The secretions are then weighed and diluted six-fold in PBS and stored at –80 °C in 250 μL aliquots.

### Urine collection and handling

First-void urine is self-collected in a urine container and transported on ice to the laboratory where it is aliquoted into a PCR urine tube (Cobas^®^, Roche Molecular Systems, Inc.) prior to later *Neisseria gonorrhoeae* and *Chlamydia trachomatis* testing by PCR.

### Foreskin collection and processing

As previously described [23], the inner aspect of the foreskin is tagged during surgery with a suture, to aid subsequent tissue orientation, and is immediately transported at ambient temperature to the laboratory. Excess foreskin tissue and obvious blood clots are trimmed off, and tissue cut into 0.25-cm^2^ pieces that are added to 500 U/ml collagenase type 1 (Gibco #17100) and 42.5 U/ml deoxyribonuclease (Invitrogen) in RPMI 1640 media. Tissues are mechanically disrupted using scissors, followed by 30 min of enzymatic digestion at 37 °C and 900 rpm on a shaker (Eppendorf Thermo mixer, Hamburg, Germany). After digestion, cell suspensions are added to 3 ml cold fetal bovine serum (FBS) and filtered through a 100-μm cell strainer (BD Biosciences, Franklin Lakes, NJ, USA). Then 30 U/ml deoxyribonuclease is added to the filtrate, cells are washed and resuspended in R10 media (comprising RPMI 1640 media with 10% heat-inactivated FBS, 10 U/ml penicillin, 10 μg/ml streptomycin, 250 ng/ml amphotericin B, and 2 mM l-glutamine; Gibco, Invitrogen, Carlsbad, CA, USA) prior to overnight resting at 37 °C under 5% CO_2_. Following overnight rest, foreskin mononuclear cells are counted using trypan blue exclusion, and approximately 10 × 10^6^ mononuclear foreskin cells plated in 500 μl R10 media.

Cells are then stained for 30 min at 4 °C with labeled monoclonal antibodies specific for subsequent flow cytometry analysis. In addition, separate tissue samples from the inner and outer foreskin are cryopreserved in 10% dimethyl sulfoxide in FBS freezing media at –150 °C and in Cryomatrix media (ThermoScientific).

## Laboratory assays

### Pseudovirus cell entry assay

A β-lactamase-viral protein R (BlaM-Vpr)-containing HIV pseudovirus has been pseudotyped with an early transmitted, CCR5-tropic, Clade A envelope [21, 24]. Virion fusion with target cells delivers BlaM-Vpr into the cytosol, and cells are then loaded with the substrate CCF2-AM, a membrane-permeant form of the fluorescent molecule CCF that contains two fluorophores, 7-hydroxy-coumarin and fluorescein, linked by a β-lactam bond. In the absence of β-lactamase, excitation of 7-hydroxycoumarin at 409 nm leads to fluorescent resonance energy transfer (FRET) to fluorescein and green light emission at 520 nm. In infected cells, β-lactamase (delivered by BlaM-Vpr) cleaves the β-lactam bond of CCF2-AM, preventing FRET, and causing blue emission (447 nm) by 7-hydroxy-coumarin. Therefore, the ratio of blue to green emission is a measure of viral fusion and cytosolic entry of HIV. This assay quantifies the number of total and infected foreskin-derived CD4^+^ T cells and/or infected cell subsets without the need for in vitro cell activation, and this readout will constitute our primary endpoint. Assays in this open-label trial will be performed by unblinded investigators.

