### Storage of biological samples

All samples will be stored at the UVRI-IAVI laboratory (Entebbe, Uganda) and/or the University of Toronto (Toronto, Canada). Samples will be stored for up to 10 years. Approvals from the University of Toronto and UVRI Research and Ethics Committees (RECs) will be sought prior to any additional testing on stored samples not listed in this protocol. Specific testing mentioned here and relevant to the study endpoints (immunofluorescence, cytokine/chemokine quantification, and microbiota profiling) will require the shipment of samples to Canada due to the lack of availability of the testing equipment within Uganda.

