### Sample size

Based on previously defined pseudovirus entry parameters into inner foreskin-derived CD4^+^ T cells [32], a sample size of 25 participants per group will provide statistical power of 80% to identify clinical approaches that reduce virus entry by ≥ 33% (based on a median virus entry of 15.1% into inner foreskin-derived CD4^+^ T cells), which is the efficacy threshold that we have deemed as sufficient to move a strategy forward.

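### The primary pseudovirus entry assay is to be performed unmasked, although open-label treatment does not require it and one control arm carries all four primary comparisons

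*Protocol article*

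**What the plan says.** The protocol article, under Pseudovirus cell entry assay, describes a fluorescence assay in which cells that virus has entered emit blue and the others green. It says of the resulting count of total and infected cells: "and this readout will constitute our primary endpoint". The next sentence is: "Assays in this open-label trial will be performed by unblinded investigators". The only reason offered is that the trial is open-label.

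Under Foreskin collection and processing, cells are stained with "labeled monoclonal antibodies specific for subsequent flow cytometry analysis". No section states how the cut-off between entered and not entered is set, or by whom.

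Under Statistical analysis, each of the four products is compared with the one untreated control group by a t test. Under Sample size, "a sample size of 25 participants per group will provide statistical power of 80" per cent for "clinical approaches that reduce virus entry by ≥ 33" per cent, "based on a median virus entry of 15.1" per cent.

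Under Storage of biological samples, the immunofluorescence, cytokine and microbiota work "will require the shipment of samples to Canada". Under Data collection and record keeping, test results are coded and any database leaving the site carries study identifiers only. That section does not describe specimen labels or say who can see the allocation.

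**The concern.** Open treatment and open laboratory reading are separate decisions, and the first does not entail the second. The primary endpoint is a proportion obtained by dividing a continuous emission signal into two classes. If the person drawing that line knows the arm, the line can move with expectation, even without intent.

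The layout of the trial makes this matter more than it would in a two-arm study. One control group is the comparator for all four products, so reading control foreskins slightly high makes every product look better at once. The Discussion says the sample size does not allow rigorous control for multiple comparisons, so there is no margin in the significance level to absorb such a shift. The same section says that one or two approaches will be taken forward. A false lead would therefore affect which product is studied next. Unlike chance error, a reading bias does not shrink as more men are enrolled.

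**Working it through.** **Inputs from the protocol article (Sample size, Statistical analysis).** 25 men per arm; control level 15.1% (a median, used here as if it were the mean); target a 33% relative reduction; power 80%; a t test of each product against control.

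**Assumptions.** The SD is not stated; the article says only "Based on previously defined pseudovirus entry parameters". The 0.05 level is given beside the explant test, and I take it as two-sided for the primary t test. The reading shifts are illustrative, since the article gives no estimate of reader variability.

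**Step 1: the stated power.** Target difference = 0.33 × 15.1 = 4.98 points. Without an SD the 80% cannot be verified, only solved backwards. With standard error = SD × √(2/25) and 48 degrees of freedom, the noncentral t gives 80% power at SD = 6.16 points (6.29 by the normal approximation). A one-sided 0.05 test would imply 6.98.

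**Step 2: difference needed for significance.** Critical t (two-sided 0.05, 48 df) is about 2.01. At SD 6.15, 2.01 × 6.15 × √(2/25) ≈ 3.5 points, which is 3.5/15.1 = 23% of the control level.

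**Step 3: effect of a differential reading shift.** Let a product have no true effect, and let controls be read b points higher than product foreskins. The noncentrality is b / (SD × √(2/25)); for b = 1 and SD 6.15 it is 1/1.74 = 0.57. A 1-point shift is 1/15.1 = 6.6% of the control level. Rejection probability per product, two-sided, with the part favouring the product in brackets:

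| Shift (points) | SD 4 | SD 6.15 | SD 8 | SD 10 |
|---|---|---|---|---|
| 0 | 5.0% (2.5%) | 5.0% (2.5%) | 5.0% (2.5%) | 5.0% (2.5%) |
| 0.5 | 7.2% (6.3%) | 5.9% (4.7%) | 5.5% (4.1%) | 5.3% (3.7%) |
| 1.0 | 13.9% (13.7%) | 8.7% (8.1%) | 7.2% (6.3%) | 6.4% (5.3%) |
| 1.5 | 25.5% (25.4%) | 13.5% (13.2%) | 10.0% (9.5%) | 8.1% (7.5%) |
| 2.0 | 41.0% (41.0%) | 20.3% (20.2%) | 13.9% (13.7%) | 10.7% (10.3%) |

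Only the SD near 6.2 agrees with the stated power. At SD 4 the power would be 99%, at SD 8 58% and at SD 10 41%. The other columns show how far the answer depends on the unknown SD.

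**Step 4: four products sharing one control.** In 200,000 simulated trials at SD 6.15, the chance that at least one ineffective product is favoured is 7.7% with no shift. It is 13.5%, 21.9%, 32.5% and 44.9% for shifts of 0.5, 1.0, 1.5 and 2.0 points.

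**Step 5: what a shift cannot do alone.** At SD 6.15 a shift must reach about 3.5 points to be significant on average, and about 5 points to imitate the 33% reduction. A 1-point shift falls well short of both; it works by adding to chance differences.

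**The case against.** The strongest reply is that the arrangement is disclosed, the assay is described as validated, and the Discussion treats every outcome except tolerability as hypothesis generating, with more rigorous testing to follow. That lowers the cost of a false lead, but it does not remove the bias, and this readout still informs which approaches are carried on.

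It can also be said that operator gating appears nowhere in the article. That is correct. It is inferred from flow cytometry and from the need for a cut-off. A fixed or automated rule may exist in the full protocol, and it would reduce the room for bias.

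Controls are circumcised at once and product arms after four weeks, so processing dates can hint at control status. This limits masking of fresh tissue but is no reason to leave coded files unmasked.

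Two stronger readings are tempting, and the documents support neither:

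- A reader might infer that all laboratory readouts are unmasked. The plural noun in the sentence allows this, but it closes the pseudovirus subsection, and the sections on the other assays are silent. An article may leave masking of secondary assays to the full protocol. The Immunofluorescence microscopy section describes objective quantification by image-analysis software, although within a depth set by the user. ELISA, PCR and 16S sequencing leave less to the reader.
- A reader might infer that a small gating shift is enough to manufacture a product effect. Step 5 shows that it is not: it raises the false-positive rate but does not on average produce significance or a 33% reduction.

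**Conclusion.** The point holds for the primary assay. The protocol article fixes unmasked performance of the assay that yields the primary endpoint, and gives no reason beyond open-label treatment, which does not require it. Because the control arm is shared, a differential reading of controls would push all four comparisons the same way.

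The direction of the harm does not depend on the SD, but its size does. An assumed 1-point shift takes the two-sided rejection rate per ineffective product from 5% to 8.7% at the back-solved SD, and to between 6.4% and 13.9% over SDs of 10 to 4. These figures show sensitivity; they do not estimate actual reader bias, which the article gives no means of judging. The conclusion rests on the inferred cut-off, the back-solved SD, a two-sided 0.05 test and the chosen shifts. It is a worthwhile, inexpensive improvement and does not by itself invalidate the trial.

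**What to change.** Replace the sentence on unblinded assays with a rule for the primary assay:

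- Samples and flow files carry a laboratory code that does not show the arm.
- Existing staff without access to the allocation list classify the coded files in mixed batches, using one prespecified cut-off rule.
- The code is broken only after the readouts are locked.

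Under Trial status and summary, enrolment began on 7 December 2017 and was expected to finish in January 2019, so the new text must not imply that earlier assays were masked. Where flow files from assays already run have been kept (the article does not say), re-read them under code. In all cases report which assays were read unmasked.

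Apply the same coding to microscopy and to the shipped samples if this is not already done. The bias risk is smaller there, as it is for ELISA, PCR and 16S.

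The cost is relabelling, a link file kept apart from the readers, and re-reading time. Sample size, assays and treatments do not change. Masking of fresh tissue will remain imperfect because of the immediate versus four-week timing; mixed-batch reading of coded files deals with most of this.

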### Foreskin explant assay

Explants maintain the physiological tissue cellular and structural milieu, providing an extra way to study HIV susceptibility at the tissue level; however, they are generally semiquantitative and so constitute a secondary endpoint in our trial. Foreskin tissue strips (2 mm) are generated through gentle maceration and inoculated with HIV-1 in the presence of phytohemagglutinin (PHA), and IL-2 added to stimulate T cell activation and proliferation in the tissue. Control samples are also cultured without HIV-1 for each time interval. At three time points during the culturing process (days 3, 7, and 10), tissue culture media is removed and p24 ELISA used to measure viral replication in HIV-infected samples. When compared with controls without PHA/IL-2, PHA/IL-2^+^ cultures exhibit a faster and earlier increase in p24 expression during the culturing process, with maximum p24 expression observed at day 3.

### Immunofluorescence microscopy

Immunofluorescence microscopy will be used to objectively quantify immune cell populations in mucosal biopsies using image analysis software (Definiens) within a user-established depth (e.g., from the foreskin epidermis). This also permits quantitative assessment of epithelial integrity, which is important in studies of HIV susceptibility using foreskin tissues snap frozen into cryomolds in optimal cutting temperature (OCT) compound.

### Multiplex ELISA for cytokine/chemokine quantification

Cytokines will be quantified by chemiluminescent multiplex ELISA (MesoScale Discovery), an assay with optimal sensitivity and reproducibility for low abundance mucosal samples and validated for use in foreskin swabs [12–14]. Genital inflammation in the female genital tract (FGT) is predefined as the presence of ≥ 3/7 inflammatory cytokines within the top quartile for that cytokine.

### Penile and FGT microbiota characterization

The penile and FGT microbiota will be assessed using barcoded universal primers to amplify V4 hypervariable regions of 16S rRNA genes. Amplicons will be purified, quantified, and pooled prior to sequencing on the Illumina MiSeq platform using the 300 bp paired-end protocol [25]. Sequence read quality will be performed using a standardized bioinformatics pipeline implemented in accordance with the National Institutes of Health Human Microbiome Project standard operating procedures. Operational taxonomic units will be clustered against the Greengenes reference database and taxonomy assigned using –utax through USEARCH, a high-throughput sequence analysis tool that is implemented in QIIME [26] (an open-source microbiome bioinformatics platform). For each sample, vectors of phylotype proportions are clustered into community state types, by computing Jensen-Shannon distances between all pairs of community states and generating a hierarchical clustering using the Jensen-Shannon distance data and Ward linkage [14, 16, 27].

### Storage of biological samples

All samples will be stored at the UVRI-IAVI laboratory (Entebbe, Uganda) and/or the University of Toronto (Toronto, Canada). Samples will be stored for up to 10 years. Approvals from the University of Toronto and UVRI Research and Ethics Committees (RECs) will be sought prior to any additional testing on stored samples not listed in this protocol. Specific testing mentioned here and relevant to the study endpoints (immunofluorescence, cytokine/chemokine quantification, and microbiota profiling) will require the shipment of samples to Canada due to the lack of availability of the testing equipment within Uganda.

### Data collection and record keeping

All study forms/laboratory reports will be reviewed for accuracy and completion prior to data entry. Changes and corrections to the forms must be initialed and dated following the principles of Good Clinical Practice. The forms and source documentation or clinical notes will be kept in a secure location and archived for at least 10 years after study completion. Source documentation and other study-related records will be held at the UVRI-IAVI research data center with personal identifiers separated from participants’ files. Data quality and integrity will be ensured through the implementation of quality control procedures during database entry including double data entry, validation, and cleaning. Queries raised during data monitoring will be directed to study investigator(s) and study staff. A file will be held at a secure, central location at the UVRI-IAVI research center site for each participant containing all the source documents and written documentation on all queries raised and how they were addressed. Source documentation will be available for review to ensure that data collected and recorded in the database and case report forms are consistent with the contents of the source documents. Participant questionnaire and test result data will be coded and securely stored at the UVRI-IAVI premises research data unit. UVRI database access is limited to study staff and restricted by login and password; any database leaving the UVRI campus for analysis purposes, either electronically or in hard copy, will contain only unique study identifiers and will have been stripped of all personal identifiers (such as name, address, date of birth, contact details, and so on).

### Statistical analysis

The impact of antimicrobial agents on a clade A HIV pseudovirus entry into foreskin-derived CD4^+^ T cells (the primary endpoint) will be assessed by comparing each product group with the untreated control group, using a standard *t* test. The same statistical approach will be used for secondary immune endpoints listed above. The readout for explant HIV infection assays will be the median quantity of HIV p24 antigen produced, and the endpoint will be the percent change in infectivity compared with the vehicle control from the same foreskin, where percentage reduction = ((control − intervention)/control) × 100. A one-sample Wilcoxon-rank test will be used to determine significance (taken as *p* < 0.05). For participants in the intervention groups, the penile bacterial load, microbiota composition, and prepuce cytokine levels will be compared between baseline and on-product visits using a paired *t* test. In female participants, cervico-vaginal bacterial load, microbiota composition, and cytokine levels will be compared between the baseline and follow-up visit using a paired *t* test. In addition, for longitudinally assessed parameters, we will perform an analysis of covariance comparing each intervention group to the control group after adjustment for baseline differences. In case of reported product noncompliance, all participants with missing data will be analyzed according to the group to which they were randomized.

Differences in microbiota biodiversity will be assessed using two biodiversity metrics: diversity (D), calculated as D = Simpson’s diversity index, and evenness (E), calculated as E = D/S, where S is richness. Evenness reflects the dominance by many (i.e., high evenness) versus few (i.e., low evenness) operational taxonomic units (OTUs), whereas richness is a measurement of the total number of unique OTUs present [28]. Differences in overall microbiota composition will be assessed visually based on family-level log-transformed absolute abundance data using nMDS and Bray-Curtis distance; differences are assessed using permutational multivariate analysis of variance (PerMANOVA) based on the log-transformed abundance data [29–31].

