### Study outcomes

The broad objectives of this clinical trial are: 1) to quantify the impact of antimicrobial agents on foreskin HIV susceptibility, immunology, and microbiota; and 2) to assess the potential impact of male partner antimicrobial use on the genital immunology and microbiota in their female sexual partner. The primary study endpoint is the percentage HIV pseudovirus entry into foreskin-derived CD4^+^ T cells in the intervention versus control arms, utilizing a validated primary clade A, R5 tropic pseudovirus entry assay [21, 22]. Secondary study endpoints include: 1) foreskin tissue density of HIV-susceptible CD4^+^ T cells; 2) the density and percentage of CD4^+^ T cell subsets (including Th17 cells) in foreskin tissue; 3) the density of Langerhans cells in foreskin tissue based on immunofluorescence microscopy; 4) the presence of foreskin inflammation using cytokine/chemokine quantitation assayed by enzyme-linked immunosorbent assay (ELISA), defined as the presence of ≥ 3/7 inflammatory cytokines within the top quartile for that cytokine; 5) foreskin microbiota composition as characterized using 16S rRNA sequencing; and 6) foreskin tissue explant HIV susceptibility, based on p24 ELISA after ex vivo incubation with a primary HIV isolate.

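### A one-sample Wilcoxon test on the explant percentage reduction leans against the products if same-foreskin pairs are used; the size depends on a variability the article does not give

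*Protocol article*

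**What the plan says.** The Protocol article lists explant infection among its secondary endpoints (Study outcomes): "foreskin tissue explant HIV susceptibility, based on p24 ELISA after ex vivo incubation with a primary HIV isolate". The section Foreskin explant assay gives the reason for that rank: "they are generally semiquantitative and so constitute a secondary endpoint in our trial".

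The Statistical analysis section then fixes four things:
- The readout: "The readout for explant HIV infection assays will be the median quantity of HIV p24 antigen produced".
- The comparator: "the endpoint will be the percent change in infectivity compared with the vehicle control from the same foreskin".
- The score and the test, with its threshold: "percentage reduction = ((control − intervention)/control) × 100. A one-sample Wilcoxon-rank test will be used to determine significance (taken as *p* < 0.05". I read this as the signed-rank test. Whether it is one- or two-sided is not stated.

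No transformation is given for this endpoint. The same section does log-transform microbiota abundance. The article gives no explant variance, no explant effect size and no explant power.

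**The concern.** The question put to the data is whether infectivity changed relative to control. The signed-rank test answers a narrower one: are the scores symmetric about zero? The two agree only if no change produces symmetric scores.

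The chosen score is one minus a ratio of two non-negative quantities, so it is squeezed on the side of benefit and stretched on the side of harm. If that asymmetry is present when a product does nothing, the test drifts towards declaring increased infectivity, and a genuine reduction is harder to show.

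The Discussion says the trial is meant to pick one or two approaches for further testing. A read-out that leans against every product could count against a useful one.

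**Working it through.** **Inputs.** Score, test and threshold come from Statistical analysis. The number of men comes from Sample size: "a sample size of 25 participants per group will provide statistical power of 80"%. That power statement concerns pseudovirus entry, so there is no explant figure to reproduce; only n = 25 is carried over. Assumed here: a two-sided test, and a log-normal intervention/control ratio with log-scale SD s, shown as a range because none is given. The 33% reduction used for power is borrowed from the primary endpoint as an illustration.

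**Step 1, bounds.** Write r = intervention p24 / control p24, so score = 100 × (1 − r), with r ≥ 0.
- r = 0.5 gives +50; r = 2 gives −100.
- r = 0.25 gives +75; r = 4 gives −300.
- r = 0.1 gives +90; r = 10 gives −900.

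**Step 2, direction.** If the two cultures from one foreskin are exchangeable under no effect, r and 1/r are equally likely. For any r > 1 the rise has magnitude r − 1 and the mirror-image fall has 1 − 1/r = (r − 1)/r, which is smaller. Negative scores therefore get the larger ranks. This needs exchangeable pairs but not log-normality. In the log-normal case the pseudo-median under no effect is −5.8% at s = 0.5, −22.1% at s = 1.0 and −48.0% at s = 1.5.

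**Step 3, size** (20,000 simulated trials per row, n = 25, exact signed-rank test; power is the chance of declaring a reduction when the median ratio is 0.67).

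| s | Null rejection, % score | of which lower / higher infectivity | Null rejection, log ratio | Power, % score v log ratio |
|---|---|---|---|---|
| 0.25 | 5.6% | 1.4 / 4.2% | 4.9% | 100 v 100% |
| 0.5 | 7.5% | 0.9 / 6.6% | 4.8% | 86.4 v 96.1% |
| 0.75 | 10.4% | 0.7 / 9.8% | 4.7% | 40.4 v 70.3% |
| 1.0 | 13.5% | 0.4 / 13.1% | 4.8% | 16.5 v 46.4% |
| 1.5 | 19.2% | 0.2 / 19.0% | 4.7% | 4.4 v 23.7% |

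A correct two-sided test would split 2.5 / 2.5%. Separate runs agree within simulation error: 10–11% null rejection at s = 0.8 with power about 33 v 65%, and 17–18% at s = 1.4 with power about 5 v 26%.

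**Step 4, if the comparator is the untreated arm.** Dividing every man's p24 by the control-arm median and keeping the one-sample test gives null rejection of 22.9, 24.2 and 26.5% on the percentage score at s = 0.5, 0.8 and 1.0. On the log ratio it is 20.3, 20.4 and 18.6%. The main error here is different: the reference is estimated from 25 other men but treated as known. A two-sample comparison between arms holds 4–5%.

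**The case against.** **Applicability.** The strongest objection is that the pair may not exist. Under Study treatment groups and randomization, products are used by the man before surgery and the controls are other, untreated men. The control cultures described under Foreskin explant assay lack HIV-1 or lack PHA/IL-2; no vehicle-treated culture is mentioned. If the comparator becomes the control arm and a two-group test is used, the one-sample problem goes away. This stands, and it governs the fix. It does not remove the point, because the article states a same-foreskin comparator, and the fuller protocol may describe such a culture.

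**Size.** No explant SD is given. Pairing within a foreskin removes between-man variation, so a small SD cannot be ruled out. At SD 0.25 total error is close to nominal and no power is lost. This stands; calling the assay semiquantitative does not establish a large SD. If only benefit is tested one-sided, there are no excess false positives, only lost power.

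**Consequence.** The Discussion treats all outcomes except tolerability as hypothesis generating, and the threshold for advancing a strategy is set on pseudovirus entry. The bias also makes false claims of benefit rarer. This stands and limits severity. It does not excuse the bias: the Discussion's caveat concerns chance findings from many comparisons, not a lean in one direction.

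**Stronger readings that a reader might infer.**
- That the score can never be symmetric under no effect. This rests on the exchangeable-pair model; against a fixed reference the score is a linear rescaling of p24, skewed only if p24 is.
- That the trial loses power for its explant target. No such target is stated.
- That explants are the only tissue-level measure. Study outcomes also lists tissue density of HIV-susceptible CD4+ T cells.
- That taking logs is always enough. Step 4 shows otherwise.

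**Conclusion.** The point holds in a limited form. For exchangeable same-foreskin pairs, the stated score and test are mismatched, and the direction of the bias, against the products, follows from the formula. Its size is conditional: negligible in total error though lopsided at a log-ratio SD of 0.25, modest at 0.5, and substantial from about 0.8 upward, where error is at least twice nominal and about half or more of the power for the illustrative 33% reduction is lost. These figures assume 25 evaluable men, a two-sided test and log-normal ratios. Without a same-foreskin pair, keeping a one-sample test against a control-arm value fails for a different and larger reason.

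Severity is minor to moderate. The documents do not support a claim that the trial's main conclusion is at risk.

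**What to change.** Revise the explant rule in Statistical analysis according to the comparator that actually exists:
- **Same-foreskin vehicle culture:** for each man take log(intervention p24) − log(control p24) and apply the signed-rank or paired t test to that difference.
- **Untreated control arm:** drop the one-sample test and compare log p24 between each product arm and the control arm, by a two-sample t or rank-sum test.

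In both cases set a fixed floor for undetectable p24; the present formula is undefined when control p24 is zero. State whether the test is one- or two-sided. Back-transform the estimate and its confidence interval to a percentage reduction for reporting only.

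The cost is a sentence or two of text and one floor value to choose and justify. The between-arm analysis needs no extra men, samples or assays, and the paired one uses cultures that already exist.
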